## Abstract

**Background:**

Following an acquired brain injury, individuals frequently experience anxiety and/or depressive symptoms. However, current treatments for these symptoms are not very effective. A promising treatment is acceptance and commitment therapy (ACT), which is a third-wave behavioural therapy. The primary goal of this therapy is not to reduce symptoms, but to improve psychological flexibility and general well-being, which may be accompanied by a reduction in symptom severity. The aim of this study is to investigate the effectiveness of an adapted ACT intervention (BrainACT) in people with acquired brain injury who experience anxiety and/or depressive symptoms.

**Methods:**

The study is a multicenter, randomized, controlled, two-arm parallel trial. In total, 94 patients who survive a stroke or traumatic brain injury will be randomized into an ACT or control (i.e. psycho-education and relaxation) intervention. The primary outcome measures are the Hospital Anxiety and Depression Scale and the Depression Anxiety Stress Scale. Outcomes will be assessed by trained assessors, blinded to treatment condition, pre-treatment, during treatment, post-treatment, and at 7 and 12 months.

**Discussion:**

This study will contribute to the existing knowledge on how to treat psychological distress following acquired brain injury. If effective, BrainACT could be implemented in clinical practice and potentially help a large number of patients with acquired brain injury.

**Trial registration:**

Dutch Trial Register, NL691, NTR 7111. Registered on 26 March 2018. https://www.trialregister.nl/trial/6916.

## Introduction

Patients with acquired brain injury (ABI) have an increased risk of developing emotional disturbances [1]. After surviving a stroke, a quarter of the patients experience depressive symptoms at 6 months post-stroke [2]; almost half of the patients who experienced a traumatic brain injury (TBI) suffer from a major depressive disorder and 38% suffer from anxiety symptoms [3]. Depression has significant effects on the health of patients with ABI. It leads to more hospitalizations, less societal participation, reduces the return-to-work rates, places a greater burden on caregivers, affects social relationships, and has a vast impact on general quality of life [4]. Moreover, anxiety and depressive symptoms have a negative influence on patient rehabilitation [5] and they increase the severity and number of reported health problems such as fatigue, memory, headaches, and concentration problems [6, 7].

Despite their high prevalence and negative consequences with a significant burden of disease, it is still not clear how to best treat post-ABI symptoms of depression and anxiety. Psychopharmacological interventions have mixed results when treating depression in stroke survivors. Additionally, stroke patients seem sensitive to the side effects of psychopharmacological medication [8]. Furthermore, antidepressants have not been shown to be more beneficial than placebo when treating depression following TBI [9]. Cognitive behavioural therapy is widely used for treating depression and anxiety, but there is no strong evidence for its post-stroke effectiveness [10, 11], and research into its effectiveness following TBI is inconclusive [12–15].

A recent type of therapy that has been proven to be effective over a wide range of clinical populations is acceptance and commitment therapy (ACT) [16–19]. ACT is a third-wave cognitive behavioural therapy, which uses commitment and behaviour change strategies to increase psychological flexibility [20]. Psychological flexibility is described as “the ability to contact the present moment more fully as a conscious human being, and to change or persist in behaviour when doing so serves valued ends” [21], p., 7. This results from a combination of the six core processes of ACT: acceptance (accepting positive and negative thoughts to situations one cannot change), defusion (disentanglement of thoughts), sense of self (separating the self from the process of thinking), mindfulness (contact with the present moment), valued living (being aware of what really matters), and committed action (taking action guided by one’s values) [21]. Although symptom reduction is not the primary treatment goal, an increase in psychological flexibility is often accompanied by a decrease in symptomatology [22, 23]. ACT is an interesting approach for people with ABI who suffer from psychological distress [24]. Instead of applying cognitive restructuring techniques as used in traditional cognitive therapy, ACT focusses on learning to accept both the negative and positive thoughts and feelings related to those circumstances that cannot be changed or controlled [25]. It enables the individual to carry out value-based behaviour while feeling distressed [25]. Higher levels of acceptance and valued living have been associated with better psychological outcomes in patients with ABI [26–28].

Currently, there is some evidence that people who developed depressive or anxiety symptoms after ABI can benefit from ACT. Majumdar and Morris [29] performed a randomized controlled trial (RCT) in which an ACT group-intervention of four weekly didactic PowerPoint sessions was compared to treatment as usual in stroke survivors. They found that people in the ACT intervention showed a significant reduction in depression and increased hopefulness and self-rated health. However, there were no differences identified in relation to anxiety or quality of life. Graham, Gillanders, Stuart, and Gouick [30] described a case study in which a stroke patient no longer experienced chest pain, had a decrease in anxiety and depressive symptoms, and improved illness perception and psychological flexibility following an ACT intervention. Whiting, Deane, McLeod, Ciarrochi and Simpson [31] performed a pilot RCT comparing an ACT group intervention with befriending therapy in patients with severe TBI. Their results show that ACT decreased the levels of anxiety and depression significantly compared to the befriending treatment. However, it could not be confirmed that the mechanism through which this decrease was elicited was psychological flexibility [31]. These findings should, however, be considered in light of the small sample size of the study and the restricted sample characteristics.

These studies provide preliminary support for the hypothesis that ACT can be effective in treating psychological distress following ABI. With the current BrainACT study, we aim to investigate whether an ACT intervention, adapted for the needs and possible cognitive deficits of people with ABI, results in decreased anxiety and depressive symptoms compared to a control intervention. Furthermore, we will examine ACT-related processes, quality of life, social participation, and the cost-effectiveness of both interventions.

Research questions addressed in the study are:
Does ACT lead to a greater reduction of depressive and anxiety symptoms in patients with ABI compared to an active control intervention (i.e. psycho-education and relaxation training)?Is ACT more cost-effective in comparison to an active control intervention?Is the (potential) reduction of anxiety and depressive symptoms mediated by an increase in psychological flexibility, acceptance, valued living, and/or cognitive defusion in the ACT group?Does ACT lead to higher levels of participation and quality of life, compared to an active control condition?

## Methods

### Study design

The design of the study is a multicenter, randomized, controlled, two-arm parallel trial in which an 8-week ACT intervention will be compared to an active control intervention, namely psycho-education combined with relaxation training. Outcome measures will be collected at baseline (T0), after 1 month (T1; during treatment), and after 3 months (T2; post-treatment). There will be follow-up measurements at 7 months (T3) and 12 months (T4). See Fig. 1 for the flow chart of the study. Ethics approval for the study has been given by the medical research ethics committee of Maastricht University Medical Centre and Maastricht University and the local committees of participating clinical centres. The study is registered in the Dutch Trial Register (TC: 7111).

**Fig. 1 Fig1:**
[figure not shown]
Design of the study: multicenter, randomized, controlled, two-arm parallel trial

### Participants

A total of 94 survivors of TBI or stroke will be recruited from rehabilitation or medical psychology departments at hospitals in the Netherlands. Patients who have been referred to a psychologist will be considered for participation. Possible participants will be screened and informed about the study by their psychologists for eligibility. Inclusion criteria are (1) having sustained any type of stroke or TBI, which is objectified by a neurologist; (2) scoring > 7 on the depression and/or anxiety subscale of the Hospital Anxiety and Depression Scale (HADS); (3) being 18 years or older; (4) having a stable use of psychotropic medication (such as antidepressants) for the duration of the study and stable use of antidepressants during 4 weeks prior to the start of the study; (5) being able to access the Internet and a computer because treatment materials such as patient videos are shown via the Internet; (6) mastering the Dutch language sufficiently to benefit from treatment; and (7) giving informed consent. Exclusion criteria are (1) history of brain injury or any neurological disorder other than a stroke and TBI; (2) pre-morbid disability as assessed by the Barthel Index (score < 19/20); (3) severe co-morbidity, for which treatment is given at the moment of inclusion, that might affect the outcome; (4) presence of a DSM 5-based mood and/or anxiety disorder for which pharmacological and/or psychological treatment was necessary during the onset of the brain injury; and (5) attendance in a previous ACT intervention for comparable problems in the year proceeding entry to the current study.

### Primary outcome measures

#### Psychological distress

The subscales of the HADS will be used to measure anxiety and depressive symptoms over the past 7 days. The scores for the scales, seven items each, range from 0 to 21 with higher scores indicating higher levels of depression or anxiety. This questionnaire has been validated in a sample of patients with TBI [32]. Furthermore, there was good internal consistency for both subscales (Cronbach α depression scale, 0.81; anxiety scale, 0.84) in patients with stroke [33]. The Depression Anxiety Stress Scales-21 (DASS-21) will be used to measure the participants’ levels of anxiety, depression, and stress. It consists of 21 items, which are rated on a 4-point Likert scale. The score ranges from 0 to 63 with higher scores indicating greater levels of depression, anxiety, or stress. The questionnaire has been validated in a sample of patients with TBI. The internal consistency was good for the three scales (Cronbach α depression scale, 0.90; stress scale, 0.89; anxiety scale. 0.82) [34]. The primary outcome is the difference between groups in change in mood and anxiety symptoms over all time points, as measured by the total scores of the respective subscales of the HADS and DASS-21.

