### Sample size calculation

The sample size calculation was performed using G*Power based on a repeated measures design. With a large effect size of 0.4, alpha value of 0.05, power value of 0.80, two groups (intervention and control), and five measurements, at least 80 participants are required. With an expected drop-out rate of 15%, 94 participants need to be recruited.

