### Statistical analysis

The statistical analysis can be divided into four parts. First, the baseline characteristics will be described. Second, between-group differences at baseline will be analysed using the chi-square test and independent samples *t* test to verify the success of randomization. Furthermore, groups will be compared on primary outcome measures at T2 using the chi-square test and independent sample *t* test. Linear mixed models for repeated measures will be used to study the differences between groups with the primary and secondary outcome measures as dependent variables. Models will include main effects of the intervention (ACT or psycho-education) and time (T0, T1, T2, T3, and T4) as categorical variables and the interaction effect of intervention and time. Baseline-adjusted mean differences between groups at each time point with 95% confidence intervals will be calculated. The effects of the intervention will be analysed according to the intention-to-treat principle. Alpha will be set at 0.05. All quantitative analyses will be conducted using SPSS software version 25 [52]. Clinically significant change will be determined on the primary outcome measures [53] to gain insight into clinical improvement on an individual level. The first step is to identify patients who “recovered” by using the cut-off scores of the primary outcome measures (HADS and DASS-21). The second step is to calculate the reliable change index, which identifies the patients with a significant improvement. Patients who both recovered and showed a significant improvement will be considered clinically significantly improved. The number of clinically significantly improved patients will be compared between interventions. The trial-based economic evaluation will involve a combination of cost-effectiveness analysis and cost-utility analysis.

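### About four HADS and DASS-21 subscales are jointly primary, with no ranking, success rule or adjustment, while the trial is sized for one test at 0.05

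*Protocol article*

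**What the plan says.** All places are in the Methods of the protocol article.

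- **Primary outcome measures, Psychological distress.** The primary outcome is worded in the singular, as one between-group difference in change covering both mood and anxiety, yet it is to be judged "as measured by the total scores of the respective subscales of the HADS and DASS-21". The HADS enters through its two subscales: "The subscales of the HADS will be used to measure anxiety and depressive symptoms over the past 7 days". The DASS-21 has three: "The internal consistency was good for the three scales". The Abstract and the Discussion also call both instruments primary and put neither first.
- **Statistical analysis.** Linear mixed models are fitted "with the primary and secondary outcome measures as dependent variables", and "Alpha will be set at 0.05". The section does not say whether this alpha applies to each test or to the set. It also plans a comparison of the primary measures at T2 and group differences at each time point.
- **Sample size calculation.** With an effect size of 0.4 and alpha 0.05, the calculation uses "power value of 0.80, two groups (intervention and control), and five measurements, at least 80 participants are required". Allowing for 15% drop-out gives 94. One alpha and one effect size are entered, so this is the power of one test.

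No section gives a testing order, a rule on how many subscales must succeed, or a division of alpha.

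**The concern.** A singular primary outcome that resolves into several scores leaves open what a positive trial is. If ACT separates from control on DASS-21 anxiety alone, the plan neither says that this establishes effectiveness nor says that it does not. The Discussion ties implementation to the intervention being effective, so the gap affects the main conclusion.

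The three statements also do not fit together. If any one subscale can carry the claim at 0.05, the error rate of the claim exceeds 5%. If alpha is split to control that rate, the 80% power in the sample size section no longer holds for a given subscale. If all subscales must succeed, the error rate is controlled, but the power to meet that criterion is below the power of a single test. Only a single primary test, or a fixed order with one test first, matches the calculation as printed.

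**Working it through.** **Inputs from the article.** Two HADS subscales; three DASS-21 subscales; named constructs mood and anxiety; alpha 0.05; effect size 0.4; power 0.80; two groups; five measurements; 80 evaluable; 15% drop-out; 94 recruited.

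**Assumed.** The correlation between subscale test statistics, which the article does not give. It is varied from 0.3 to 0.8, with independence as the upper limit.

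**1. The plan's own figure.** The article names G*Power and a repeated-measures design but not the routine. The figure of 80 is reproduced by the repeated-measures MANOVA group-by-time interaction:

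- noncentrality λ = f² × N = 0.4² × 80 = 12.8; df = 4 and 80 − 5 = 75
- power at alpha 0.05 = 0.803; with N = 79 it is 0.797, so 80 is the minimum
- drop-out: 80 / 0.85 = 94.1, printed as 94

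Other routines with effect 0.4 and within-person correlation 0.5 give 32 (between-factors) or 10 (univariate interaction). The printed number is therefore consistent with one four-degree-of-freedom interaction test at 0.05.

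**2. Number of tests.** Depression and anxiety on two instruments: 2 × 2 = 4. Adding DASS-21 stress gives 5.

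**3. Chance of at least one false positive, each test at 0.05.** If independent:

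- four tests: 1 − 0.95⁴ = 0.185
- five tests: 1 − 0.95⁵ = 0.226

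With equally correlated 4-df interaction tests (simulation, 300,000 draws, large-sample chi-square):

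| Correlation | Four tests | Five tests |
|---|---|---|
| 0.3 | 17.6% | 21.4% |
| 0.5 | 16.0% | 18.9% |
| 0.7 | 13.6% | 15.5% |
| 0.8 | 12.0% | 13.3% |

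Against 5%, that is 12.0 / 5 = 2.4 to 17.6 / 5 = 3.5 times nominal for four tests, and 13.3 / 5 = 2.7 to 21.4 / 5 = 4.3 times for five. The T2 tests and per-time-point estimates are not counted.

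**4. Power with 80 evaluable if several subscales stay primary.** The model is that of step 1. The strictest step uses 0.05 / K. The last column is the average power per subscale under Holm (simulation), if every subscale carries the planned effect.

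| Primary subscales | Strictest alpha | Power at that step | Average Holm power |
|---|---|---|---|
| 1 | 0.05 | 80% | not applicable |
| 2 | 0.025 | 71% | about 77% |
| 4 | 0.0125 | 61% | about 71% |
| 5 | 0.01 | 58% | about 69% |

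For 80% power at the strictest step, four subscales need 108 evaluable (108 / 0.85 = 127.1, so 128 recruited). Five need 112 (112 / 0.85 = 131.8, so 132 recruited).

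**The case against.** **No any-one rule is written.** This is the strongest point, and it stands as a limit on the claim. A reader might infer that the trial may declare success on any single subscale and so has a demonstrated false-positive rate of 16-20%. The article does not say so. If all subscales had to succeed, there would be no inflation. The rates above are conditional on a reading that the text leaves open.

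**The analysis plan may settle it.** A multiplicity rule often sits there, and that document is not shown. But the article itself selects the primary scores, sets the alpha and sizes the trial, and these do not agree. A rule elsewhere that split alpha would make the printed power wrong for a given subscale.

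**Four tests, not five, is the natural count.** Stress is not among the named constructs, so the four-test column is the better guide. One could also count three, because the article gives the DASS-21 only a total range of 0 to 63. One DASS-21 total plus two HADS subscales gives 1 − 0.95³ = 14.3% if independent. The word for subscales in the definition favours four or five.

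**Power is not lost on every view.** Under Holm, the chance of succeeding on at least one subscale can exceed 80% when all carry the planned effect. What falls is the power for any given subscale.

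**Dilution is not supported.** Entry requires a score above 7 "on the depression and/or anxiety subscale of the Hospital Anxiety and Depression Scale", so some patients will be elevated on one subscale only. It is tempting to add that such patients cannot improve on the other and that power drops further. The documents do not support this. A score of 7 or below on a 0 to 21 scale still leaves room to fall, the DASS-21 has no entry threshold, and the share of such patients is not given. Nor does the article say that the effect of 0.4 applies only to elevated patients.

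**Conclusion.** The point holds in this form: about four subscale scores are jointly primary, with no ranking, success rule, order or adjustment, and the sample size supports one test at 0.05. That much is in the text and needs no assumption.

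The size is conditional. It requires that a result on any one subscale be taken as effectiveness, and it depends on an assumed correlation. Since the HADS and DASS-21 each measure depression and anxiety, fairly high correlations are plausible, which points to the lower part of the range. A single headline figure would claim more than the article allows.

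This should be settled before unblinding, because it decides what counts as a positive trial.

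**What to change.** Before unblinding, state in the protocol and analysis plan one of the following.

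1. **One primary score tested at 0.05**, for example one named HADS subscale or the HADS total. The remaining HADS and DASS-21 subscales become secondary. Which score to name is the sponsor's choice; the HADS total would need defining, since the article describes only its subscales.
2. **A fixed testing order**, in which each subscale is tested at 0.05 only if the one before it succeeded.
3. **Several primary subscales with Holm.** The sample size section then has to restate the power, using the figures in the working for the number of subscales kept.

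The text should also say whether DASS-21 stress belongs to the primary set.

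Options 1 and 2 keep 80 evaluable and 94 recruited, with 80% power for the first or only primary test. All three are changes of wording and need no further data; more patients would be needed only if 80% power at Holm's strictest step were wanted. The cost is that some subscales lose primary status or, under option 3, that the stated power becomes less favourable.

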#### Cost effectiveness

Two questionnaires will be used to measure cost effectiveness: the 5-level Euroqol-5 dimensions (EQ-5D-5 L) and a 16-item cost questionnaire. The EQ-5D-5 L consists of five questions measuring health status. The dimensions covered are mobility, self-care, daily activities (such as work, housework, study, and leisure activities), pain or discomfort, and anxiety or depression. These domains are rated as “no problem”, “slight problem”, “‘moderate problem”, “severe problem”, or “unable to do”. Consequently, the EQ-5D-5 L can distinguish between different health states. For each of the different states a weight is contributed based on the valuation given by the general population [35]. The healthcare costs of participants will be measured with a self-report cost questionnaire, which is constructed to collect cost data from a societal perspective, based on the steps described by Thorn et al. [36]. The cost questionnaire used in this study is based on a questionnaire used in the study of Kootker et al. [11]. Several questions are altered based on response patterns and analyses in this prior study. The primary cost-effectiveness outcome is the change in the amount of care used between groups over all time points, as measured by the total scores of the cost-questionnaire and the EQ-5D-5 L.

### Secondary outcome measures

#### Participation

The Utrecht Scale for Evaluation of Rehabilitation-Participation (USER-P) will be used to measure three aspects of participation: frequency of behaviours, participation restrictions experienced due to health condition, and satisfaction with participation. The frequency scale measures the objective level of participation, while the restrictions and satisfaction scales offer an insight into the subjective rating of participation. The questionnaire consists of 31 items. A score ranging from 0 to 100 is calculated for each scale. Higher scores indicate more participation, less restriction, and more satisfaction. It is a valid and reliable measure for patients with ABI; the internal consistency is good (Cronbach α = 0.70–0.91) [37].

